## STUDY SCHEMA

[figure not shown]

**Primary Endpoint:** esophageal quality of life (FACT-E) at 2 weeks following RT

## **1.0 INTRODUCTION**

### **1.1 Background**

Palliative thoracic radiotherapy is an effective modality for symptom prevention and improvement in patients with metastatic non-small cell lung cancer. For a subset of these patients with good performance status (ECOG 0-1), a meta-analysis found that employing doses of 35 Gy10 and higher (e.g. 30 Gy in 10 fractions) through a standard conventional antero-posterior/postero-anterior (APPA) approach was associated with a modest survival benefit at 1-year, compared to lower doses. This however, was at the cost of an increased rate of esophagitis within 3 months (1). Esophagitis can lead to pain, weight loss, and hospital admissions, and overall can reduce quality of life. In some cases, specifically in the setting of stage III NSCLC, severe esophagitis after treatment has been associated with inferior overall survival (2), perhaps due to malnutrition.

In the modern era, there is wider availability of advanced radiotherapy techniques (e.g. CT-simulation, IMRT, arc-based therapy), allowing for increased conformality and sparing of organs at risk (OARs), allowing for conformal avoidance of organs at risk, such as the esophagus. Esophageal sparing has been employed for stage III NSCLC with early promising results (3,4), but to our knowledge has not been formally tested in the palliative setting. The goal of this study is to conduct a multi-institutional randomized phase III clinical trial comparing standard palliative treatment (APPA), using doses of 20 Gy in 5 fractions or 30 Gy in 10 fractions, versus the same dose using esophageal-sparing IMRT (ES-IMRT).

## **2.0 OBJECTIVES**

To assess the impact of ES-IMRT versus standard palliative RT on quality of life, survival, toxicity and cost-effectiveness in patients with metastatic/locally advanced lung cancer, in the year after RT.

### **2.1 Endpoints**

#### **Primary Endpoint:**

1. Esophageal quality of life
  - Measured by the Esophageal Cancer Subscale (ECS) of the FACT-E

#### **Secondary Endpoints:**

1. Pulmonary and General Quality of life
  - Pulmonary quality of life measured by the Lung Cancer Subscale (LCS) of the FACT-L
  - General quality of life measured by the FACT-G and the EQ-5D
2. Overall survival
  - Defined as time from randomization to death from any cause.
3. Toxicity
  - Assessed by the NCI-CTC v.4
4. Cost Effectiveness
5. Dosimetric comparisons of plans in both arms.

### **3.0 STUDY DESIGN**

This study is designed as a randomized phase III study. Patients will be randomized between standard of care palliative thoracic RT vs. ES-IMRT.

Patients will be stratified by intended dose prescriptions of 30 Gy in 10 fractions or 20 Gy in 5 fractions, and the choice of dose is pre-specified before randomization.

Patients will be randomized in a 1:1 ratio to either:

**Arm 1: Standard Radiotherapy (delivered as 3-D conformal radiotherapy without esophageal sparing).** An APPA technique is preferred.

**Arm 2: Esophageal Sparing Radiotherapy using IMRT.** Patients will receive the same pre-specified dose, but with esophageal sparing.

**In either arm, radiotherapy must begin no later than 2 weeks from the time of randomization, although treatment as early as possible is highly encouraged.**

### **4.0 PATIENT SELECTION**

#### **4.1 Inclusion Criteria**

1. AJCC 7th edition stage IV NSCLC or stage III not eligible for curative intent treatment
2. Intended to receive palliative radiotherapy to the thorax, to a dose of 30 Gy

in 10 fractions or 20 Gy in 5 fractions. In either treatment arm, at least **5 cm of the esophagus** should be in the intended treatment field.

3. Willingness and ability to provide informed consent
4. ECOG performance status 0-3
5. Age 18 years or older
6. Prior or planned systemic treatment (chemotherapy, immunotherapy, targeted agents) is permissible at the discretion of the treating medical oncologist, provided that no systemic treatment is given within 2 weeks prior to RT, concurrent with RT, or within a 2-week period post RT.
7. Concurrent palliative RT to other metastatic sites is permissible other than the stomach and/or liver
8. Life expectancy > 3 months

#### 4.2 Exclusion Criteria

1. Prior thoracic RT
2. Serious medical comorbidities, which in the opinion of the radiation oncologist preclude the delivery of RT
3. Pregnant or lactating women
4. Inability to attend the full course of RT or planned follow up/survey responses.
5. Congenital abnormalities of the esophagus or severe disorders of the esophagus (e.g. achalasia)

### **5.0 PRE-TREATMENT EVALUATION**

The following are mandatory:

- i. History and physical examination, with documentation of weight and performance status (ECOG)
- ii. CT chest within 3 months.
- iii. Bone scan and brain imaging (CT or MRI) are recommended if there are signs or symptoms consistent with metastases at those sites
- iv. Negative serum or urine pregnancy test for women of child-bearing age
- v. Histological confirmation of NSCLC malignancy
- vi. Informed consent

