### 6.04 Target Volumes and Organs at Risk (OAR)

Prior to randomization, all patients will have the following contours delineated on the 4D-CT dataset.

- The gross tumor volume (**GTV**) is defined as pathologically confirmed or radiographically suspicious (>1cm in diameter, and/or PET avid) tumor and lymph nodes that the radiation oncologist wishes to treat for palliation. **It is not required to treat all intrathoracic disease, and this is left to the judgment of the radiation oncologist.** Lung windows will be used to contour the primary tumor and mediastinal windows for nodal disease.
- Motion management: given that the standard approach in this patient population does not include explicit motion management, options are as follows:

- Option 1: Combine GTVs from different phases of the respiratory cycle (i.e. end exhalation and inhalation) to form an internal GTV (**iGTV**).
- Option 2: Contour GTV on the untagged average or maximum intensity projection to form the iGTV.
- The use of an expansion for microscopic disease is optional and should reflect standard institutional practices. If used, it should be no more than 5 mm and may be adjusted for natural boundaries for spread. If a microscopic expansion is not used, the iGTV can be expanded by 5-8 mm to form PTV. If the microscopic expansion is used, then a further 5 mm expansion to PTV is allowed.
- An esophageal sparing PTV (**ES-PTV**) will be created by subtracting the esophagus\_ring (see below) from PTV.

The following OARs will be contoured:

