### 6.5 Registration procedure and Data Collection:

#### Registration/Randomization Procedure

1. Call the coordinating centre at the Cancer Clinical Research Unit [contact] [name]) of London Health Sciences Centre (LHSC) to notify of new randomization and ask for the next patient ID number.
2. Complete the Enrollment form in REDCap prior to randomization. Signed letter of information to be completed and uploaded on to the REDCap database.

3. Notify the coordinating centre that you have completed the enrollment form and uploaded the required documents.
4. If the patient is eligible the coordinating centre will confirm via email and provide the randomization arm.

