### 10.6 Data Safety Monitoring Committee

The DSMC will be independent and consist of a statistician and two content experts uninvolved in the trial. The DSMC will meet every six months after study initiation to review toxicity outcomes. If any grade 3-5 toxicity is reported, the DSMC will review cases notes to determine if such toxicity is related to treatment. If the DSMC deems that toxicity rates are excessive (>25% grade 3 toxicity or >5% grade 4/5 toxicity) then the DSMC can, at its discretion, recommend cessation of the trial or dose adjustment. The DSMC may consider removing a dose level if the rate of clinically significant change in ECS (defined as 2 point change from baseline) occurs in <10% of patients in the control arm. If the DSMC decides that review of toxicity data by email (rather than in-person DSMC meetings) is sufficient because of low toxicity rates, this will be acceptable.

Interim analysis: the DSMC will conduct one interim analysis once 30 patients are accrued. The rationale for this analysis is to ensure that trial accrual is proceeding in a timely manner and to terminate the trial if early stopping rules are met. In this analysis, the DSMC will be blinded to the identity of each treatment arm, but ECS data and OS will be presented for each arm. The DSMC will recommend stopping the trial if there is a statistically significant difference with  $p < 0.001$  using Student's t-test (Haybrittle-Peto stopping rule) in ECS or OS between the two arms. Furthermore, if the measured differences in esophageal QOL are substantially different than estimated in the sample size calculation, the DSMC can recommend increasing or decreasing the target accrual in order to maintain statistical power.

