## Appendix 2 – Follow-up schedule

|                       | pre-RT                       | 2 weeks post RT | *4, 8 weeks post RT            | Months 3, 6, 12        |
|-----------------------|------------------------------|-----------------|--------------------------------|------------------------|
| History and physical, | X                            | X               | Only if clinic visit is booked | X                      |
| *Toxicity scoring     | X                            | X               | X                              | X                      |
| CT chest              | X                            |                 |                                | Suggested and optional |
| Bone scan             | Recommended if bony symptoms |                 |                                |                        |
| CT or MRI brain       | Recommended if CNS symptoms  |                 |                                |                        |
| *FACT-E and FACT-L    | X                            | X               | X                              | X                      |
| *EQ-5D                | X                            | X               | X                              | X                      |

\* QoL forms and toxicity scoring may also be completed via telephone for all follow up visits (but not preferred) if patient prefers or is unable to attend clinic. For non-English patients, a fluent family member, staff, or professional translator may assist with completion of the questionnaire. The FACT-E and FACT-L are also available in the following languages (contact the coordinating centre or [www.facit.org](http://www.facit.org) for these):

Chinese (simplified or traditional), Dutch, French, German, Hungarian, Italian, Japanese, Polish, Spanish

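### Baseline quality-of-life forms are tied to the start of radiotherapy, not to randomization, so the text lets them be completed after the arm is known

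*Protocol*

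**What the plan says.** **What is listed before treatment.** Protocol section 5.0 begins "The following are mandatory" and gives six items: history and physical, chest CT, bone and brain imaging where symptoms suggest it, a pregnancy test, histology, and consent. No questionnaire is among them.

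**Where baseline quality of life appears.** Section 9.0 asks for the questionnaires at each visit, but every visit it lists follows radiotherapy. The only instruction to collect a baseline is the Appendix 2 table, where the "FACT-E and FACT-L" row and the EQ-5D row carry an X under the pre-RT column.

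**The gap between allocation and treatment.** Section 3.0 says that "radiotherapy must begin no later than 2 weeks from the time of randomization". In section 6.5 the final registration step reads "If the patient is eligible the coordinating centre will confirm via email and provide the randomization arm". The only blinding described is in section 10.6, for the interim analysis: "the DSMC will be blinded to the identity of each treatment arm".

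**What must come before randomization.** The choice of dose (sections 3.0 and 6.0), the contours (section 6.04: "all patients will have the following contours delineated on the 4D-CT dataset"), the signed APPA fields (end of section 6.04) and the registration paperwork (section 6.5: "Complete the Enrollment form in REDCap prior to randomization") are all fixed before randomization. The questionnaires are not named among these.

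**Where baseline ECS is used.** Section 10.6 lets the DSMC consider removing a dose level when a clinically significant ECS change, "defined as 2 point change from baseline", occurs in fewer than 10% of control patients. Section 10.5 tests the primary endpoint on 2-week scores by t-test. It analyses the other quality-of-life endpoints by linear mixed-effects models without saying how baseline enters.

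**The concern.** A baseline is useful because randomization makes the arms comparable on it. That holds only if it is measured before allocation can influence the answer. A patient who already knows whether the plan spares the esophagus may answer more hopefully or more gloomily, and the baseline then becomes a post-randomization variable. The FACT forms ask about the past 7 days (Appendix 4), so a form completed in the second of the two permitted weeks could cover only days after allocation.

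The stake is every result that treats the pre-RT score as a neutral starting point: change scores, baseline-adjusted contrasts, mixed models that use baseline, and the DSMC's count of control patients who change by 2 points. This is a data-collection matter. An analysis plan cannot recover a pre-allocation score that was never taken.

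**Working it through.** **1. The plan's own figure.** Section 10.4 gives effect size 0.65, two-sided alpha 0.05, power 80% and 15% non-response.

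- n per arm = 2 × (1.960 + 0.842)² / 0.65² = 15.70 / 0.4225 = 37.2, rounded up to 38.
- 38 / 0.85 = 44.7, rounded up to 45 per arm, or 90 in total. The stated figure reproduces. (Solving with the t distribution gives 38.14, hence 39, then 46 per arm and 92, which is immaterial here.)
- The timing of the baseline does not enter this calculation.

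**2. The order of events the text allows.** Contours, APPA fields, dose and enrollment form are completed; the arm is released; up to 2 weeks pass; radiotherapy starts. Appendix 2 is satisfied by a form completed anywhere before that last step, including after the arm is released.

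**3. Which analyses use baseline.**

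- Primary t-test on 2-week scores (10.5): no baseline term, so bias from this source is 0.
- Interim t-test on ECS (10.6): no baseline term stated.
- DSMC dose-level rule (10.6): uses baseline, within the control arm only.
- Mixed models (10.5): exposed only if baseline enters as a covariate or as a response.
- EQ-5D utilities (10.5): exposed only if the analysis starts from, or adjusts for, the baseline value.

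**4. Hypothetical size for a between-arm contrast.** Let b be the mean between-arm difference in baseline ECS caused by knowing the arm. No document gives b; assume 0.5 to 1.0 point.

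- Change score: the bias has size b, so 0.5 to 1.0 point.
- Baseline-adjusted contrast with assumed slope 0.5: 0.5 × b = 0.25 to 0.5 point.
- b is an arm-level mean. If only a fraction f of baselines is taken after allocation and each shifts by s, then b = f × s. With f = 0.5 and s = 0.5 to 1.0, b falls to 0.25 to 0.5 and the adjusted bias to 0.125 to 0.25.

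To show what such a shift would do to a test, take the SD implied by section 10.4 (2/0.65 = 3.08 to 3/0.65 = 4.62), 38 evaluable per arm, and an assumed baseline-to-follow-up correlation r of 0.3 to 0.7.

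- Change score: SE = SD × √(2(1 − r)) × √(2/38). Worst corner: 3.08 × √0.6 × 0.229 = 0.547; 1.0 / 0.547 = 1.83; two-sided type I error 45%. Mildest corner: 4.62 × √1.4 × 0.229 = 1.25; 0.5 / 1.25 = 0.40; type I error 7%.
- Adjusted contrast: bias r × b, SE = SD × √(1 − r²) × √(2/38). Type I error runs from about 5% to 28%.

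**5. The DSMC rule.** This is a rate within one arm, so step 4 does not describe it. At 30 accrued with an even split there are about 15 control patients: 1 of 15 is 6.7% and 2 of 15 is 13.3%, so one patient reclassified by a shifted baseline can cross the 10% line. Within one dose level the count would be smaller still. Direction is not fixed: if the change is read as a worsening, a gloomier baseline lowers the count and a rosier one raises it.

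**The case against.** The strongest reply is that pre-RT in Appendix 2 plausibly means the baseline work-up. The same column holds the history and physical, which section 5.0 requires with ECOG status. ECOG is an eligibility criterion and so is settled before the arm is released. Section 3.0 also urges early treatment, which shortens the window, and the REDCap enrollment form, whose content is not shown, may already carry the questionnaires. This stands as a reason to doubt how often late baselines would occur. It does not remove the fact that the wording permits them.

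Three stronger readings are tempting and should be resisted.

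- **That the primary result is biased.** Section 10.4 speaks of an ECS change, so a reader might infer a change-from-baseline primary analysis. Section 10.5 fixes the test on 2-week scores alone.
- **That baseline quality of life is optional and may be skipped.** Section 5.0 omits it, but the X in Appendix 2 is unqualified, whereas bone scan and brain imaging in the same column are only recommended. Section 5.0 is not a full schedule: it also omits baseline toxicity scoring, which Appendix 2 marks. Skipping the forms would depart from the schedule. Nor would a missing baseline always drop a patient: the primary test does not need it, and a mixed model with baseline as a repeated response keeps the patient.
- **That the bias is a known share of the 2 to 3 points called clinically relevant.** Any such percentage comes wholly from assumed shifts and from between-arm baseline analyses that the protocol does not specify.

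**Conclusion.** The point holds as a defect of timing. The text ties the baseline FACT-E, FACT-L and EQ-5D to radiotherapy and not to randomization, and so permits collection after the arm is known. That the trial is open-label is inferred from release of the arm and the absence of any patient or investigator blinding; the protocol does not use the term.

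The primary comparison and the sample size are untouched. The exposure is confined to a discretionary DSMC rule within the control arm and to secondary analyses that use baseline, whose form the protocol leaves open. The documents do not allow the bias to be sized; the 0.5 to 1.0 point and 0.25 to 0.5 point figures, and the error rates that go with them, are hypothetical and shrink with the share of baselines actually taken late. It merits correction because the change is nearly free and the loss cannot be repaired once a patient has been randomized.

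**What to change.** - In Appendix 2, change the timing of the first FACT-E, FACT-L and EQ-5D from pre-RT to before randomization.
- In section 5.0, add the three questionnaires to the mandatory list with the same timing.
- In section 6.5, steps 2 to 4, have the site record completion on the enrollment form and the coordinating centre confirm it before releasing the arm.

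The cost is protocol wording and one extra check at a registration step that already exists. Planning CT, contours and signed fields are already required before randomization, so no new visit or form is needed, and the target stays at 90 patients.

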## **6.0 TREATMENT PLAN**

In either treatment arm, concurrent chemotherapy, targeted therapy, and/or immunotherapy is not permitted within the 2 weeks prior to RT, during RT, or 2 weeks following RT. Permissible doses are 30 Gy in 10 fractions or 20 Gy in 5 fractions, and this must be specified prior to randomization.

### **6.01 Test Cases**

Prior to trial activation, each participating site must complete two test planning cases to ensure protocol compliance. These cases will be provided in anonymized form by secure FTP transfer. For further details, please see section 6.4.

### **6.02 Immobilization and positioning**

Treatment will be set up using reproducible positioning, verified using an on-line

protocol, for all patients in this study. Immobilization may include items such as a chest board, vac-lok bag and/or double leg immobilizer, as per individual institutional practice.

### 6.03 Radiation Simulation

For all patients, a 4D-CT will be performed with 3 mm thick contiguous CT slices and the scanned volume should encompass at least C5 to below the diaphragm. Simulation will be in the treatment position (e.g. arms placed above the head if possible). Oral contrast to aid in the delineation of the esophagus (i.e. esophacat) is optional at the time of simulation. IV contrast to improve the delineation of target volumes and organs at risk is optional.

### 6.04 Target Volumes and Organs at Risk (OAR)

Prior to randomization, all patients will have the following contours delineated on the 4D-CT dataset.

- The gross tumor volume (**GTV**) is defined as pathologically confirmed or radiographically suspicious (>1cm in diameter, and/or PET avid) tumor and lymph nodes that the radiation oncologist wishes to treat for palliation. **It is not required to treat all intrathoracic disease, and this is left to the judgment of the radiation oncologist.** Lung windows will be used to contour the primary tumor and mediastinal windows for nodal disease.
- Motion management: given that the standard approach in this patient population does not include explicit motion management, options are as follows:

- Option 1: Combine GTVs from different phases of the respiratory cycle (i.e. end exhalation and inhalation) to form an internal GTV (**iGTV**).
- Option 2: Contour GTV on the untagged average or maximum intensity projection to form the iGTV.
- The use of an expansion for microscopic disease is optional and should reflect standard institutional practices. If used, it should be no more than 5 mm and may be adjusted for natural boundaries for spread. If a microscopic expansion is not used, the iGTV can be expanded by 5-8 mm to form PTV. If the microscopic expansion is used, then a further 5 mm expansion to PTV is allowed.
- An esophageal sparing PTV (**ES-PTV**) will be created by subtracting the esophagus\_ring (see below) from PTV.

The following OARs will be contoured:

#### **Right and Left Lung**

- contoured on the lung window, excluding trachea and GTV

#### **Lung\_evaluation**

- both lungs minus GTV

#### **Spinal cord**

- based on bony limits of the spinal canal, and extending 10 cm above and below the PTV

#### **Esophagus**

- contoured on the mediastinal window from cricoid to the GE junction on the average intensity projection. Should include mucosa, muscular, and adventitial layers.

#### **Esophagus\_ring**

- a 5 mm isotropic expansion around the esophagus to facilitate sparing in the optimization process

#### **Heart**

- contoured from the apex of the heart to the inferior aspect of the origination of the ascending aorta

**Prior to randomization, the intended APPA fields from Arm 1 will be placed on the planning CT, and that plan will be signed by the radiation oncologist. Those fields will be used as the basis for safe toxicity parameters for Arm 2. If the patient is randomized to Arm 1, the signed fields are to be treated without further modification.**

#### **6.1 Standard Arm (Arm 1)**

RT for patients in the standard arm should adhere to the principles of palliative RT, with goals of alleviating symptoms or preventing potential complications. An APPA parallel-opposed pair (POP) beam arrangement is favored wherever possible. POP fields will be placed to encompass PTV (without regard for ES-PTV). Multileaf collimator blocks may be placed to protect OARs (i.e. lung) at the discretion of the treating physician.

Dosimetric parameters for Arm 1 are as follows:

- **The field edge should be >5 mm from the edge of PTV.** If the oncologist feels that the resulting field size is larger than required, then smaller target volumes should be defined. It is not necessary to contour areas of disease that are not being treated.
- The maximum effective field size is recommended to be limited to **225 cm^2** but is at the discretion of the treating radiation Oncologist. The maximum hot spot is limited to no more than a 2 cm^3 contiguous volume receiving 115% or more of the prescribed dose.

The treating physician, dosimetrist or physicist will record the following parameters from the APPA fields:

- length of esophagus in the field (defined as the length of esophagus receiving >50% of the prescription dose at any point along its circumference). This is required to be at least 5 cm for enrollment.
- maximum and mean esophageal dose
- maximum cord dose
- PTV D95 (the dose to the hottest 95% of the PTV).
- Lung eval V16 (if 30 Gy in 10 fractions used) or V13 (if 20 Gy in 5 fractions used).
  - The V16 and V13 are used to approximate the V20 used for conventional fractionations. BED values are as follows:
    - When V20 is used with a prescription dose of 60 Gy in 30

fractions, the corresponding BED, for the 20 Gy in 30 fractions received by lung eval, is 24.4 Gy3

- When V16 is used with a prescription dose of 30 Gy in 10 fractions, the corresponding BED, for the 16 Gy in 10 fractions received by lung eval, is 24.5 Gy3
- When V13 is used with a prescription dose of 20 Gy in 5 fractions, the corresponding BED, for the 13 Gy in 5 fractions received by lung eval, is 24.2 Gy3

